## Demographic information

Evaluation of the demographic and other baseline data, including clinical medical history, will be performed on the safety evaluation set. Sample size, mean, standard deviation, median, minimum and maximum values for continuous data, and frequency and proportion for categorical data, will be presented. For comparison between the treatment arms, the independent two-sample t-test or the Wilcoxon rank sum test for continuous data, and the Chi-square test or Fisher’s exact test for categorical data, will be used to evaluate statistical significance.

## 7.6. Interim analysis

Interim analysis will not be performed.

# Ethico-legal aspect of the trial

## Responsibilities of the investigator

The investigator will be responsible for conducting this study at the study site with which they are affiliated. The investigator will ensure that the study is conducted according to the protocol, the ethical principles as per the Declaration of Helsinki, the GCP regulations of ICH (ICH Topic E6, 1996), and the local regulations. The investigator must particularly make sure that only the subjects who provide informed consent are included in the study.

## Subject information and consent

Written consent for study participation is an unconditional and absolute prerequisite for a subject’s participation in the study. Before a subject is accepted onto the study, written consent by the subject or the subject’s parents or legal guardian is required. Before consent is obtained, the investigator must provide the appropriate information to the subject or subject’s legal guardian. The subject information sheet, used for obtaining a subject’s consent, must be in the subject’s mother tongue and prepared by the sponsor in accordance with ICH GCP (ICH Topic E6, 1996). The investigator must also orally explain all aspects of the study, apart from the information given in the written subject information sheet, in layman’s terms (i.e. in language that is easy for non-medical personnel to understand).

After the explanation, the investigator and subject must individually sign and date the subject consent form.

The signed and dated consent forms must be kept at the investigator’s study site and stored safely for easy access for monitoring, check-up, and audits. A copy of the signed and dated consent form, along with a copy of the subject information sheet, must be provided to the subject before study participation.

If important new information arises that can affect the subject’s consent, the sponsor must revise the subject consent form and the subject information sheet and resubmit both documents to the IRB for review and approval. The revised information, after approval, must be provided to each subject, and each subject must sign and date the revised consent form after the investigator has explained the changes from the previous version.

## Subject identification and confidentiality

Once consent is obtained, each subject will be assigned a unique identification number. This number will be used for the duration of the study, as well as during data processing.

Subject information collected during the study period will also be stored using this number. Only the investigator may associate the subject with the subject information regarding this study, using the identification list stored at the study site. Subject confidentiality must be strictly maintained during any review of the original data for document verification by a monitoring agent, during a check-up, or during an audit by health authorities.

The law on information protection and privacy protection covers all stages of obtaining, relaying, processing, and storing a subject’s personal information. The subject must be clearly informed of, and give consent to, information processing methods as per the local legislation. Sensitive information gathered in this study, including information regarding the health of the subjects, will be stored for up to three years after study termination, and thereafter will be destroyed appropriately.

## Subject compensation and insurance

All subjects participating in this study will be protected by insurance appropriate for the local situation. The compensation policy, in case of damage due to this study, will be approved by the IRB.

## Institutional review board (IRB)

Before commencement of the study at each site, the protocol, the case report form, and all documents provided to the subjects, including the subject information sheet, must be submitted to the IRB for approval.

The approval letter from the IRB must be kept in the investigator site file for the relevant study site, and a copy must be kept in the clinical trial basic document file of the sponsor or proxy organization. The study must not begin before IRB approval. Once approval is obtained, a document stating the date of approval, the review board member list, and the voter list must be conveyed. The approval document must clearly state the study, the protocol version, the subject information sheet, and the consent version. If possible, meeting minutes must also be conveyed. Changes to the study must also be submitted to the IRB before implementation (refer to Section 9.5). The relevant safety information during the study period must be submitted to the IRB, in accordance with the regulations and policies.

## Government authorities

In accordance with local law, the relevant regulatory authorities must be notified of the study, and this protocol and other relevant documents (product information for the investigational products, the subject information sheet, and the subject consent form) must be submitted.

# Clinical Trial Management

## Management of case report forms

The purpose of case report forms is to collect necessary information, in accordance with the study protocol, in a manner that is complete, accurate, easily recognized, and time-saving. Information on case report forms must correspond with information on evidence documents.

The information collected during this study must be recorded on case report forms, and, if applicable, adverse event safety report forms, and conveyed to either the sponsor or the sponsor’s proxy. The conveyed information will be processed, evaluated, and stored anonymously in accordance with information protection regulations.

The investigator must confirm that the case report forms and other related documents have been relayed to the sponsor or relevant proxy anonymously.

Data must be recorded in full in the case report forms in an easily legible manner in black or blue ballpoint pen that can be used for official documentation. All changes or amendments must be made and countersigned by the investigator, with the date of the change / amendment recorded. Errors must be documented legibly and must not be corrected using correction tapes. The investigator must record the reason for any change / amendment in important documentation item.

Blank spaces for information omitted from the case report form must be struck out to prevent unnecessary queries.

As these documents are essential to clinical trials, case report forms must be managed so that they are adequate for submission for auditing purposes by government authorities.

## Evidence and subject files

The investigator must preserve all paper or electronic files related to the subjects participating in this study (e.g. medical files and original copies of medical records). These files include demographic data and medical records of the subjects and must be recorded as completely as possible. In particular, the following information must be discernable from these files:

- - Name of subject.
  - Birth date.
  - Gender.
  - Demographic information.
  - Past and present medical history.
  - Past and present medication history (including changes during study period).
  - Trial identification information.
  - Date of study enrollment (date of written consent).
  - Subject number during study period.
  - Dates of site visits.
  - Medical tests, as pre-defined by the protocol, or other clinical findings.
  - All adverse events.
  - Study end date.
  - If applicable, the date of discontinuation of the study or the investigational products, and the reason for discontinuation.

This subject file will be used for the personal identification of each subject.

All documents, including printed results of values measured by an automated device, radiological data, electrocardiogram records, and laboratory test results, will be kept within the file. These documents should at least contain the subject number and information on the date of treatment. If possible, data must be directly printed from the device used for the evaluation or measurement. Data that cannot be printed from an automated device will be recorded in person. If necessary, any medical evaluation based on these records must also be recorded, as well as the investigator’s signature and the date.

Some information can be directly recorded in the case report forms (or survey or logs), rather than in the original medical files, if the original file (paper or electronic) that corresponds to that information does not exist. In this case, the information in the case report forms serves as evidence. If the information in the case report form serves as evidence, the protocol must clearly and completely state what type of information belongs to such a case. If the information in the case report form is not explicitly stated as evidence, it must be stated in the subject’s medical file.

## Storage of the investigator file and data

The investigator will be provided with the investigator site file at the time of study commencement. This file will include all documents necessary to conduct this study and must be regularly updated to maintain a complete record until study termination. This file must be accessible to the monitoring agent for review, and readily available for the sponsor’s review and audit by the health authorities. In accordance with the Enforcement Rule for Medicinal Product Safety Article 30 Clause 12, the file must be kept for three years after study termination. The stored document will include the subject identification list and subject consent. If storage of the investigator site file becomes impossible at the respective site, the investigator must alert the sponsor to this. The investigator will protect the personal information of the subjects in accordance with the local laws and regulations. The personal information for each subject will be processed anonymously using coded numbers, such that age, gender, and other personal information cannot be recognized. Identifiable data will be stored with limited access to ensure confidentiality of the records. Study data will be viewed and studied anonymously for research purposes only and can be published if necessary. In the event that the data are published, the personal information of the subjects will be kept confidential.

All original files related to the subjects (medical records) must be stored for the longer of the duration mandated by either the law regarding the clinical trial site (hospital, research organization, or clinic) or the ICH clinical trial management regulation (GCP). Medical records must not be destroyed before written consent is obtained from the sponsor.

## Monitoring quality control, government audit

This study will be monitored according to the Korean Food and Drug Administration and Clinical Trial Management Protocol by ICH (ICH topic E6, 1996, and KGCP). Monitoring will be conducted by a monitoring agent designated by the sponsor. The monitoring agent for each study site will regularly visit the site. The sponsor or sponsor’s proxy, as well as the health authorities, must be allowed to audit all documents related to the study, as well as other data from the study sites, including the investigator site file, the completed case report forms, the investigational products, medical records / subject files, etc.

The protocol, information acquisition process for each step, data handling and management, and the clinical trial result report are subject to quality assurance to monitor whether the relevant laws are being upheld. An audit may be conducted at a random time point during or after the study period in order to ensure the validity and verity of the information related to this study.

## Change of protocol

If the protocol is to be changed, the change should be documented on documents related to protocol change (plan of change). For major changes (e.g. changes to a significant portion or important changes), the documentation must be provided to the related parties and to the IRB for approval. The major changes can only be implemented after approval.

Minor protocol changes, including administrative changes, will be documented and stored with the sponsor and at study sites, and will be submitted to the IRB or the health authority according to the relevant policies.

All changes that may impact a subject’s consent must be applied after renewed consent from the subjects (refer to Section 8.2).

## Principles of clinical study reports and data presentation

## Clinical study report

The clinical study report will be drawn up after study termination, based on the principal investigator’s advice, etc. and in accordance with the ICH E3 guideline.

## Data presentation

The first presentation regarding this study will include analysis of the primary endpoint based on data collected from all study sites. The investigator or investigator’s proxy should notify the sponsor if there is any plan to publish or present data related to this study. All data to be published or presented (as an abstract, press release, oral presentation, etc.) should be sent to the sponsor for review (either the entirety or part of a draft). The sponsor will not object to, or deny, any presentation, but reserves the right to delay the timing of the presentation for protection of intellectual property or based on their commercialization strategy.

# Appendices

## Appendix 1. Study schedule

| Schedule | Screening & Washout period | | Treatment & Follow-up Period* | |
| --- | --- | --- | --- | --- |
|  | Screening1 | Randomization | | End of Study |
| Weeks | -2 - 0 | 0 | | 12 |
| Day of visit | -14 - 1 | 1 | | 84-87 |
| Visit category | V1 | V2 | | V3 |
| Consent |  |  | |  |
| Screening number assignment |  |  | |  |
| Inclusion / exclusion criteria |  |  | |  |
| Demographic information / medical history / medication history |  |  | |  |
| Physical examination 2 | (including weight) |  | |  |
| Vital signs3 |  |  | |  |
| X-ray (lesion)4 |  |  | |  |
| Pain VAS5 | - |  | |  |
| Randomization |  |  | |  |
| Blood test |  |  | |  |
| Blood chemistry test 6 |  |  | |  |
| Hematological test 7 |  |  | |  |
| Pregnancy test8 |  |  | |  |
| Drug administration |  |  | |  |
| Distribution of study drug / ancillary drug / rescue drug |  |  | |  |
| Collection of study drug / ancillary drug / rescue drug |  |  | |  |
| LDQ, GSRS, EQ-5D |  |  | |  |
| Distribution of subject log |  |  | |  |
| Collection of subject log |  |  | |  |
| Confirmation of co-administered drugs |  |  | |  |
| Adverse event monitoring |  |  | |  |

1. If additional washout is not needed, screening and randomization can be conducted on Day 1.
2. Height (history), weight (measured). Weight measured only at visit 1.
3. Blood pressure, pulse rate, respiration rate.
4. Not conducted if there is an X-ray result of the lesion taken within 6 months.
5. Conducted only at visit 2 and not at visit 1.
6. ALT, AST, BUN, creatinine, glucose, total bilirubin.
7. CBC (hemoglobin, hematocrit, RBC count, WBC with differential count, platelet count).
8. Conducted only in women of childbearing potential.

- **Additional visit**: Additional visits may be conducted if follow-up observation of adverse events is needed.

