## Exclusion criteria

1. Persons who are participating in a clinical study or have participated in a clinical study within the last 30 days (participation is based on the date of final investigational product administration).
2. Persons with a history of abuse of alcohol or other drugs within 6 months prior to screening.
3. Persons who drink 21 standard drinks or more per week (generally, 55 mL of soju is equated to 200 mL of beer or 30 mL of spirits).
4. Persons with a history of peptic ulcer disease with complications (bleeding, perforation, penetration, and gastric outlet obstruction) within the last 5 years.
5. Persons with a history of peptic ulcer disease without complications within 6 months prior to screening visit or persons with active peptic ulcer disease.
6. Persons who have been infected with helicobacter but did not undergo eradication therapy.
7. Persons with a known history of gastroesophageal reflux disease.
8. Persons with a confirmed diagnosis or clinical suspicion of the following arthropathies that may affect safety and efficacy evaluation: septic arthritis, inflammatory arthropathy such as rheumatoid arthritis, gout, recurrent pseudopain, Paget’s disease, fracture, ochronosis, acromegaly, hemochromatosis, Wilson’s disease, primary osteomalacia, and Ehlers Danlos Syndrome and other genetic collagen disorders.
9. Persons with surgery planned during the study period.
10. Persons with a history of gastrointestinal cancer.
11. Persons with a GI disorder due to a malfunction in drug absorption.
12. Persons with gastrointestinal bleeding, cerebrovascular bleeding, other bleeding disorders, or severe hematological disorders.
13. Persons with moderate to severe hepatic impairment (Child Pugh Class II or higher).
14. Persons with a history of severe heart failure or coronary artery bypass graft (CABG).
15. Persons with severe renal impairment (CrCl <30 mL / min).
16. Persons with severe hypertension (SBP ≥160 mmHg or DBP ≥100 mmHg) refractory to treatment.
17. Persons with a history of allergy to components of the investigational product.
18. Persons with hypersensitivity or allergy to other NSAIDs or PPIs.
19. Subjects who received contraindicated drug or therapy within a pre-specified period prior to study participation (Section 5.3.2).
20. Patients who are receiving contraindicated co-administration drug (Section 5.3.3).
21. Patients who have a history of surgery on the osteoarthritic joint within the past 1 year.

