2. Hypersensitivity: symptoms of shock (dyspnea, hypotension, bradycardia, diaphoresis, edema, etc), PIE syndrome (pulmonary infiltration with eosinophilia: fever, wheeze, cough, sputum), anaphylactic reaction, hives, rash, and pruritis.
3. Gastrointestinal: hematemesis, peptic ulcers, perforation, gastric discomfort, gastric pain, abdominal pain, nausea, vomiting, decreased appetite, dyspepsia, heartburn, diarrhea, constipation, stomatitis, distension, malena, thirst, esophagitis, gastritis, glossitis, belching, flatulence, coffee-ground vomit, pancreatitis, colitis, exacerbation of inflammatory bowel disease (ulcerative colitis, Crohn’s disease), and ulcerative stomatitis.
4. Hematological: agranulocytosis, neutrophilia, granulocytopenia, pancytopenia, leukopenia, thrombocytopenia, aplastic anemia, hemolytic anemia, platelet dysfunction (prolongation of the bleeding time), and lymphadenitis.
5. Hepatic: GOT and GPT elevation, jaundice, hepatitis, liver failure, and cholestatis.
6. Renal: renal dysfunction, glomerular nephritis, hematuria, interstitial nephritis, renal syndrome, renal papillary necrosis, proteinuria, renal failure, and oliguria / polyuria.
7. Central nervous system:

- Somnolence and cognitive dysfunction; rarely dizziness, headache, paresthesia, decreased libido, fatigue, depression, dream abnormalities, inability to concentrate, disorientation, insomnia, myalgia, muscle weakness, agitation, anxiety, confusion, hallucination, nervousness, lethargy, and myasthenia gravis.

- Aseptic meningitis (discontinue the drug and consult physicians if the following symptoms occur: severe headache, nausea, vomiting, neck stiffness, fever, and / or an altered level of consciousness).

1. Respiratory: dyspnea, asthma, bronchospasm, eosinophilic pneumonitis, pneumonia, pulmonary edema, and decreased respiration.
2. Dermatological: pruritis, ecchymosis, rash, eczema, sweating, purpura, photosensitivity, alopecia, redness, toxic epidermal necrolysis (TEN), erythema multiforme, erythema nodosum, fixed drug eruption, lichen sclerosis, porphyria cutanea tarda, exfoliative dermatitis, and bullous skin reaction.
3. Sensory: tinnitus, hearing disorder, and vision disorder.
4. Metabolic and nutritional: edema, fluid retention, hyperglycemia, hypoglycemia, hyperkalemia, and hyperuricemia.
5. Infection: diverticulitis, infection, and sepsis.

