   6. Skin and appendages: bullous dermatitis and ecchymosis; occasional rash, alopecia, dermatitis, nail disease, photosensitivity reactions, pruritus, erythematous rash, maculopapular rash, skin disorders, dry skin, increased sweating, urticaria, erythema multiforme, exfoliative dermatitis, Stevens-Johnson syndrome, toxic epidermal necrolysis (Lyell syndrome), eczema, lipoma, and allergic dermatitis; rarely petechiae, dandruff, and drug rash with eosinophilia and systemic symptom (DRESS).
   7. Cardiovascular: arrhythmia, ventricular hypertrophy, malignant hypertension, hypertension, angina, unstable angina, coronary artery disease, myocardial infarction, heart failure, congestive heart failure, palpitations, tachycardia, stroke, aortic regurgitation, hematoma, and sinus bradycardia; rarely syncope, ventricular fibrillation, pulmonary embolism, cerebrovascular spasm, peripheral gangrene, thrombophlebitis, phlebitis, arrhythmic embolism, and cerebral hemorrhage.
   8. Infection: upper respiratory infection, erysipelas, wound infection, and gingival infection; occasional herpes simplex, herpes zoster, bacterial infection, fungal infection, soft tissue infection, viral infection, moniliasis, genital moniliasis, and otitis media.
   9. Reproductive: breast tenderness and menopausal symptoms; occasional breast fibromatosis, thoracic neoplasm (female), chest pain (female), menstrual pain, menstrual disorder, cervical bleeding, vaginitis, prostate disorder, and ovarian cysts.
   10. Ear: occasional hearing loss, ear pain, tinnitus, and hearing difficulties.
   11. Hepatobiliary: occasional liver dysfunction, ALT elevation, AST elevation, γ-GTP elevation, ALP increase, and urine urobilinogen positivity; rarely cholelithiasis, hepatitis, jaundice, liver failure, fulminant hepatitis, and liver necrosis.
   12. Metabolic and nutritional: increased sodium concentration and increased potassium concentration, occasional BUN increase, CPK increase, diabetes, hypercholesterolemia, hyperglycemia, NPN increase, creatinine increase, alkaline phosphatase increase, weight gain, decreased appetite, and LDH increase; rarely hypoglycemia and hyponatremia.
   13. Musculoskeletal: ganglionic pain; occasional arthralgia, arthrosis, skeletal disorder, myalgia, neck tension, fasciitis, tendonitis, myositis, leg spasm, fracture, and tendon tear; rarely back pain and muscle spasm.

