## Contraindications for the control drug

1. Patients with hypersensitivity or a history of hypersensitivity to this drug or its components.
2. Patients with an allergic reaction to sulfonamides.
3. Patients with a history of asthma, acute rhinitis, nasal polyps, angioedema, urticaria, or allergic reaction to aspirin or other NSAIDs (including COX-2 inhibitors).
4. Patients with severe hepatic impairment.
5. Patients with severe renal impairment (CrCl <30 mL / min).
6. Patients with active peptic ulcer disease or GI bleeding.
7. Patients with inflammatory bowel disease, such as Crohn’s disease or ulcerative colitis.
8. Patients with congestive heart failure (NYHA II-IV).
9. Patients with confirmed ischemic heart disease, peripheral arterial disease, and / or cerebrovascular disease.
10. Pregnant women, or women of childbearing age.
11. Lactating women.
12. Patients being treated for post-carotid arterial bypass graft (CABG) pain.
13. Patients with hyperkalemia.
14. This drug contains lactose. Therefore, patients with genetic conditions such as galactose intolerance, Lapp lactase deficiency, or glucose-galactose malabsorption should not be given this drug.

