17. Two large, controlled, clinical trials of a different COX-2 selective NSAID for the treatment of pain in the first 10-14 days following CABG surgery found an increased incidence of myocardial infarction and stroke.
18. Clinical tests (urine analysis, blood test, renal function test, liver function test, electrocardiocram, fecal occult blood test, etc.) must be conducted regularly or as needed. If abnormal result is found, appropriate management including temporary or permanent discontinuation of this drug must be implemented.
19. This drug should not be co-administered with NSAIDs other than low-dose aspirin (325 mg/day or less).
20. Patients who experience dizziness or somnolence after taking this drug should avoid driving or operating heavy machinery.
21. This drug does not exert any effect on platelet function and should not be used as a substitute for aspirin in preventing cardiovascular events. Patients receiving antiplatelet therapy should not discontinue it when given this drug.
22. It must be noted that NSAID therapy is a symptomatic treatment rather than curative treatment.
23. Cross-sensitivity: a patient with sensitivity to an NSAID may exhibit sensitivity to other NSAIDs.
24. Patients with autoimmune disease (e.g. systemic lupus erythematosus (SLE) and mixed connective tissue disease (MCTD) patients) may be at an increased risk of asceptic meningitis when given this drug.
25. Administration of this drug to diabetic patients or concomitant administration of this drug with agents that increase serum potassium concentration may cause hyperkalemia. Therefore, in such cases, regular monitoring of potassium level is necessary.
26. Temporary infertility has been reported in female patients on long-term NSAID therapy.

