#### Table 2. List of Laboratory Safety Tests

| **Hematology** | **Serum Chemistry** |
| --- | --- |
| Hemoglobin (Hgb) | Alanine aminotransferase (ALT) |
| Hematocrit (Hct) | Aspartate aminotransferase (AST) |
| RBC count | Blood urea nitrogen (BUN) |
| Platelet | Creatinine |
| WBC with differential count | Glucose |
|  | Total bilirubin |

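### Potassium is never scheduled and hyperkalaemia is not an exclusion, although the protocol contraindicates the control drug in hyperkalaemia

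*Protocol*

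**What the plan says.** **Contraindication.** Section 5.3.5.2 (control drug), item 13, reads "Patients with hyperkalemia".

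**Monitoring.** The general precautions for the control drug (Section 5.3.5.4, item 25) warn of hyperkalaemia in diabetic patients and in patients also taking agents that raise serum potassium. They add that "in such cases, regular monitoring of potassium level is necessary".

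**Known effect.** Section 5.3.5.1 includes "increased sodium concentration and increased potassium concentration" among the metabolic events for celecoxib. For naproxen, Section 5.3.4.1 lists "edema, fluid retention, hyperglycemia, hypoglycemia, hyperkalemia, and hyperuricemia", and its table for the combination tablet places hyperkalaemia under rare events.

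**Scheduled tests.** Appendix 1, footnote 6 gives the chemistry panel as "ALT, AST, BUN, creatinine, glucose, total bilirubin". Table 2, "List of Laboratory Safety Tests", names the same six chemistry analytes. The Synopsis schedules chemistry at V1 and V3 only.

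**Eligibility.** None of the 23 exclusion criteria in Section 4.3.2 mentions hyperkalaemia or potassium. Diabetes is not excluded. Potassium-raising agents as a class are not on the prohibited lists in Sections 5.3.2 and 5.3.3. Section 5.3.3 discourages non-study drugs in general but lets the investigator give any drug judged medically necessary.

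**The concern.** The protocol states that one of its two study drugs should not be given to patients with a particular laboratory abnormality. It then neither measures that abnormality nor names it as a reason for exclusion. Allocation is 1:1 and double-blind (Section 7.2), so an investigator cannot apply celecoxib-specific checks only to subjects on celecoxib. Any such check has to be written for every subject.

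Two things are at stake:

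- **Safety.** A subject with unrecognised hyperkalaemia could be enrolled and given a drug contraindicated for that subject. There is then no scheduled visit between randomisation and week 12.
- **Safety data.** The laboratory tables in Section 7.5.3 would hold no scheduled potassium values, although raised potassium is listed for both active treatments.

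**Working it through.** The protocol states no figure to reproduce here. The check compares its sections and then puts a scale on the consequence.

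**1. Two contraindications that rest directly on a chemistry value, side by side**

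| Control-drug contraindication (Section 5.3.5.2) | Matching exclusion (Section 4.3.2) | Scheduled test (Table 2; Appendix 1, footnote 6) |
| --- | --- | --- |
| Item 5: severe renal impairment, CrCl below 30 mL/min | Yes, item 15, same threshold | Yes, creatinine (and BUN) |
| Item 13: hyperkalaemia | None | None |

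The protocol carries the first through to eligibility and testing, and does neither for the second. Table 2 and footnote 6 are separate lists that agree on all six analytes, so the absence of potassium is not an artefact of one broken table.

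**2. What the partial safeguards cover**

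- Medical and medication history (Sections 6.1 and 6.2) and exclusion 23 (investigator's judgement) act only on hyperkalaemia that is already known.
- Exclusions 14 and 15, with creatinine and BUN, address severe heart failure, previous coronary bypass surgery and renal function. They do not measure potassium.
- Additional visits (Section 6.1) allow blood sampling, but at the investigator's discretion and mainly to follow up adverse events.

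Hyperkalaemia that nobody knows about at screening remains uncovered.

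**3. Scheduled potassium values:** 0 of 106 subjects at V1 and 0 of 106 at V3.

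**4. Subjects randomised with unrecognised hyperkalaemia.** The protocol gives no rate. Assume 0.1–1% after the existing exclusions.

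- Whole trial: 106 × 0.001 = 0.106 to 106 × 0.01 = 1.06.
- Celecoxib arm: 53 × 0.001 = 0.053 to 53 × 0.01 = 0.53.

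**5. On-treatment events: a ceiling from the Korean post-marketing survey in Section 5.3.5.1.** The survey reports 338 events among 5,648 cases. The itemised events add up to

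155 + 54 + 33 + 13 + 12 + 12 + 10 + 7 + 5 + 5 + (4 × 2) + (17 × 1) = 331,

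and none of them is hyperkalaemia. That leaves 338 − 331 = 7 events unnamed. If all seven were hyperkalaemia, the rate would be 7 / 5,648 = 0.124%, or 53 × 0.00124 ≈ 0.07 cases in the celecoxib arm. These are reported events, not measured potassium, so the figure bounds what was reported and not what occurred.

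**6. Subjects in the monitoring group named in Section 5.3.5.4, item 25.** If 15–30% are diabetic (an assumption), 106 × 0.15 = 15.9 to 106 × 0.30 = 31.8, so about 16–32 subjects, before counting users of potassium-raising agents.

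**7. Cost of measuring:** 106 × 2 = 212 assays, plus one per screen failure.

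**The case against.** Section 5.3.5 reads largely as reproduced product labelling. The control-drug dosing section, for example, includes regimens for indications not under study. A labelled contraindication applies to patients known to have the condition and does not by itself call for a screening assay. History and exclusion 23 deal with known cases, the plausible number of unknown ones is below one, and the rates behind that number are assumed. This stands as a reason to rate the point low. It does not close the gap, because the protocol did turn the comparable renal contraindication into both a criterion and a test.

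Other control-drug contraindications also lack a full matching exclusion: sulfonamide allergy, inflammatory bowel disease, milder heart failure (NYHA II), ischaemic heart, peripheral arterial or cerebrovascular disease, and the lactose-related genetic conditions. That is true, and it shows that the list in Section 5.3.5.2 was not systematically carried into Section 4.3.2. It does not make this omission acceptable.

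A V3 value comes when treatment ends and cannot protect a subject during the 12 weeks. This is also correct. The protection comes from the V1 result, while V3 supplies safety data. The laboratory analysis in Section 7.5.3 promises no electrolyte results, so nothing planned is lost. The point there is that the planned tables would not address a listed effect of both drugs.

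Finally, an exclusion without a threshold could operate differently across 10 sites with their own reference ranges. The fix should therefore state a threshold and a repeat-test rule.

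**Conclusion.** The concern holds, as a minor point. The facts rest on the text alone: a stated contraindication, two concordant test lists without potassium, and 23 exclusions that do not name hyperkalaemia. Confidence in the omission is high.

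The expected effect is small. Under the assumed 0.1–1% rate, about 0.05–0.5 subjects would receive celecoxib despite unrecognised hyperkalaemia. The only bound from the protocol's own data is about 0.07 reported on-treatment events in 53 subjects. The LDQ endpoint, the non-inferiority analysis and the sample size are untouched. The argument for change is that a contraindication the protocol itself states can be checked at almost no cost, not that many events are expected.

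**What to change.** 1. Add serum potassium to Table 2 and to Appendix 1, footnote 6, at V1 and V3, using the existing blood draws.
2. Add hyperkalaemia to the exclusion criteria in Section 4.3.2 and the Synopsis, for example as potassium above the site laboratory's upper limit confirmed on a repeat sample. State that the investigator's latitude over out-of-range results in inclusion criterion 5 does not apply to it.
3. Require review of the V1 potassium result before the first dose. Appendix 1, footnote 1 allows screening and randomisation on the same day.
4. Report potassium in the laboratory tables of Section 7.5.3.

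On-treatment checks in diabetic subjects and users of potassium-raising agents can remain a recommendation to investigators, with no extra draw required.

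**Cost:** about 212 assays plus one per screen failure, occasional screen failures for hyperkalaemia (with a repeat sample if the confirmation rule is adopted), and a short delay when screening and randomisation would otherwise fall on one day. No added scheduled visit is needed, and the sample size does not change.
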